### Implementation {16c}

Trained study staff will be responsible for the management of product implementation which will include the initial deployment of product, subsequent removal, and replacement at 4-week intervals.

## Assignment of interventions: blinding

### Who will be blinded {17a}

The Sponsor, study PI, and staff will not be blinded to cluster assignment (SR delivery channel). There will be no placebo integrated into the study design, as the SR intervention will have already been evaluated for efficacy under controlled conditions.

### Procedure for unblinding if needed {17b}

Not applicable—study will not be blinded.

## Data collection and management

### Plans for assessment and collection of outcomes {18a}

#### Mapping of the study area and census measurements

Mapping will be conducted in all 48 clusters; 70% refugee and 30% host villages will be considered. These will be selected based on government structures and population size of the clusters and proximity to the refugee villages. All HHs in each cluster will be invited to participate in the study. Verbal consent will be obtained and within each cluster, individual HHs will be enumerated and all structures in the study area will be mapped using GPS coordinates and assigned a unique HIN. A questionnaire will be administered to measure housing structure and HH member demographic characteristics. This includes housing construction, and number of inhabitants and their age.

Following mapping, clusters will be delineated and randomly allocated to delivery channels using standard statistical software (e.g., SAS, STATA, or R).

#### Enrollment of the cohort

A cohort of children aged ≥ 6 months to ≤ 59 months will be enrolled within each cluster to assess the effectiveness of the SR product against the contemporaneous control and in additional clusters to estimate effectiveness using programmatic delivery systems. HHs will be randomly selected from the master list of HHs obtained during ramp-up phase mapping to achieve the desired sample size.

Selected HHs based on cluster maps will be visited and if a child is present, the study will be explained and consent obtained from the child’s primary caregiver before screening for eligibility and enrolling him/her in the study. All eligible children in a selected HH will be invited to participate. (See above for a more complete description of the consent process.) At enrollment, the study team will have a list of all age-eligible children in each HH selected. These data will have come from the initial mapping and census of the study clusters. At the time of participant recruitment, the tablet will randomly select one of the age-eligible children for the field staff to screen for inclusion and exclusion criteria, which includes a hemoglobin test. Prior to screening, the team will obtain parental/caregiver consent. If there are no eligible children in the HH after screening, a new HH will be randomly selected from the HH listing exercise (mapping and census).

At enrollment, the age and gender of the child will be recorded and the parent/guardian (as needed) will be asked about the use of ITNs and anti-malarial drugs. Contact information, as available, will be captured. A fingerstick blood sample will be taken for a malaria RDT, and a hemoglobin level will be evaluated in a capillary sample using the HemoCue device**.** The study team will work with local health partners and the district health department providing iCCM to make sure children in need of iron supplements and antihelminths are managed according to national protocols and coordinate any referrals or follow-ups as needed. If the screened child does not meet the inclusion criteria, the tablet will randomly select another child from the remaining age-eligible children in the same house. The process will continue until one of the children is successfully enrolled.

All children enrolled in the study will be provided an ITN. This will allow us to measure the added benefit of SR product above that provided by currently recommended preventive measures. In addition, a blood sample will be taken for a RDT for all participants enrolled in the cohort to be used as a baseline data measure. All participants (regardless of RDT results) will be provided a treatment dose of artemisinin-combination treatment (ACT) AL at the start of the study prior to receiving SR, to clear any prepatent or patent malaria parasites, unless they have recently been treated (within the last 2 weeks). Participants will be treated according to RDT results throughout the study period, according to national protocols.

The enrollment period will take approximately 1 month, during which time incidence of malaria disease in study clusters will be measured prior to the deployment of the study product.

#### Enrollment to receive the SR product

The study product will be explained to the head of HH, as described in the main protocol, and consent for participation will be obtained prior to start of study. No routine blood samples will be sought.

#### Follow-up of the cohort

All efforts to overlay the commencement of enrollment with the start of the malaria transmission season will occur; however, programmatic timelines may not allow for perfect alignment. The 12-month follow-up period will ensure estimating potential changes in malaria incidence during anticipated seasonal malaria transmission peaks.

The distribution of the SR will occur after enrollment. At this time, cohort participants will be presumptively cleared of parasites with a treatment dose of AL unless they have recently been treated (within the last 2 weeks). This will be done so that the incidence of malaria infection following study product deployment can be measured.

Participants enrolled in the cohort will be followed every 2 weeks for malaria infection during the 12-month period after the study product has been distributed. All cohort participants and HH residents will also be informed to come to the nearest health facility for unscheduled sick visits, as needed. If the participant presents with a history of fever in the last 48 h, a RDT will be performed and AL will be administered if the RDT is positive for malaria.

Every 2 weeks, study team data collectors will visit the enrolled HHs. At each data collection HH visit, the parent/guardian will be asked about the recent use of ITNs and other vector control interventions as well as recent history of illness, recent travels outside the HH, and recent use of anti-malarial drugs.

During the first scheduled HH visit, a blood sample will be taken for malaria RDT (Monthly Visit #1). During the second scheduled HH visit, a blood sample will only be taken if the participant has a recent history of fever (Monthly Visit #2). The total blood volume for samples at each visit will not exceed 500 mli. A second blood sample may be taken for hemoglobin testing during follow-up only if the data collection/clinical team suspects anemia in participating children.

Cohort participants who test positive for malaria by RDT will be treated with ACTs free of charge according to national treatment guidelines. Hospital fees will not be paid by the study unless the illness or injury is due to study products or procedures as determined by the health facility physician and the study coordinator, in coordination with the study’s local PI. If there is illness or injury due to study products or procedures, fees will be paid for care at the government health facilities or District or Provincial Hospital according to the clinical trial insurance policy of the study.

When participants are not available for a follow-up visit, there will be a grace period/ “window” for each follow-up visit. There will be an allowable range of + / − 3 days for scheduled follow-up data collection home visits to occur.

In total, it is estimated that approximately 2.5 h will be needed from research participants at the start of the study (for the HH mapping, structures and HH enrollment, parasite clearance, and distribution of ITN). Throughout the study, 50 min will be needed for the VHT and study personnel arms (for the follow-up visits and SR placement), while approximately 1 h may be needed for the voucher arm as they will be walking to the central location to redeem their SR.

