### Relevant concomitant care permitted or prohibited during the trial {11d}

While the standard-of-care for clinical management of malaria and vector control interventions (e.g., ITNs, IRS) will not be withheld in any of the distribution channels, these interventions will be monitored and recorded throughout the study. ITNs continue to be distributed through mass campaigns every 2 years with the latest distribution conducted in early December 2023 in Yumbe District, where the Bidibidi Refugee Settlement is located. ITNs are also distributed regularly to pregnant women during antenatal and postnatal care services at health facilities in the Bidibidi Refugee Settlement, and to children under five during expanded immunization programs. IRS started in December 2022 and is expected to occur annually, with the latest conducted in December 2023. At enrollment, eligible children will be provided a treatment dose of artemether-lumefantrine (AL) free of charge for malaria parasite clearance and a new ITN. In addition, study participants will be provided treatment for malaria infection throughout the follow-up period. Participants will be encouraged to continue ITN use and not instructed to avoid alternative vector control tools (e.g., coils, topicals, aerosol sprays, repellents) which will allow for an estimation of the SR effect assuming all other measures are still occurring for malaria prevention, essentially providing insight on an additive benefit above that provided by currently recommended WHO malaria preventive measures.

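### The clearing AL dose is tied to enrolment in two places and, most naturally, to SR distribution in a third; if it is given at enrolment, infections acquired before SR can be counted as post-deployment infections

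*Protocol article*

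**What the plan says.** The protocol article times the clearing dose in four places.

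- Relevant concomitant care {11d}: "At enrollment, eligible children will be provided a treatment dose of artemether-lumefantrine (AL) free of charge for malaria parasite clearance and a new ITN". No exemption is stated.
- Enrollment of the cohort: the dose is given whatever the RDT result, "at the start of the study prior to receiving SR, to clear any prepatent or patent malaria parasites", with an exemption for children treated in the preceding 2 weeks.
- Follow-up of the cohort, on the start of follow-up: "The distribution of the SR will occur after enrollment. At this time, cohort participants will be presumptively cleared of parasites with a treatment dose". The same 2-week exemption follows, and the stated purpose is to make incidence after product deployment measurable.
- Follow-up of the cohort, on the time asked of participants: the start-of-study tasks are listed as "for the HH mapping, structures and HH enrollment, parasite clearance, and distribution of ITN". SR placement is counted separately, under time needed during the study.

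On the calendar, Enrollment of the cohort says: "The enrollment period will take approximately 1 month, during which time incidence of malaria disease in study clusters will be measured prior to the deployment", meaning SR deployment. Outcomes {12} defines the primary outcome as RDT-confirmed infection after SR deployment. Follow-up of the cohort runs for 12 months from SR distribution, with a routine RDT once a month and fever-triggered tests otherwise. An RDT is described at enrolment; none is described at SR deployment.

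**The concern.** The clearing dose sets time zero. It lets the trial treat a later positive RDT as an infection acquired with the product in place. That works only if little time passes between clearance and first SR installation.

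If AL is given at enrolment and SR comes later, a child can be cleared, infected again before any product is hung, and found positive at the first follow-up RDT. That infection would be counted as a post-deployment event, against both the outcome definition and the stated purpose of the dose. If AL is given when SR is distributed, the problem is close to nil apart from exempt children. The article does not settle which of these applies.

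The mid-point rule in Methods for additional analyses {20b} adds a smaller problem: if the visit before the first positive test is the enrolment visit, the imputed infection time can fall before SR.

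**Working it through.** **The passages side by side.** Section {11d} and the list of start-of-study tasks put clearance at enrolment. The follow-up sentence puts it, on its natural reading, at SR distribution, which is said to come after enrolment. The enrolment section, which requires only that AL precede SR, fits either. The conflict is therefore two places against one.

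**Inputs from the documents.** Incidence r = 0.5 to 1.0 per person-year, between-cluster coefficient of variation 0.40, 10% loss, 16 clusters per arm, 40 households per cluster in the precision statement and 45 recruited (Sample size {14}); 90% Wald interval (Statistical methods {20a}); about 1 month of enrolment (Enrollment of the cohort). One child per household gives 16 × 45 = 720 per arm.

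**Assumed.** The gap g from AL to first SR for each child, which the documents do not give: 7, 14 and 30 days, the last being the whole enrolment month. Post-treatment protection is ignored, which makes the figures too high.

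**The plan's own precision figure.** SE(log HR) = √[(2/16)(0.40² + 1/E)], with E = 40 × 0.9 × (1 − e^(−r)) first infections per cluster.

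- r = 0.5: E = 14.2, SE = 0.170, 90% limits exp(±1.645 × 0.170) = 0.76 to 1.32.
- r = 1.0: E = 22.8, SE = 0.160, 90% limits 0.77 to 1.30.

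The plan states lower limits of 0.75 to 0.77 and upper limits of 1.30 to 1.33, so its precision is essentially reproduced. It does not depend on AL timing, and serves here as a yardstick.

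**Children infected between AL and SR.** p = 1 − exp(−r × g/365.25).

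| Gap | r = 0.5 | r = 1.0 |
|---|---|---|
| 7 days | 1.0% | 1.9% |
| 14 days | 1.9% | 3.8% |
| 30 days | 4.0% | 7.9% |

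At 30 days this is 720 × 0.0402 = 29 to 720 × 0.0789 = 57 children per arm.

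**Effect on the HR if the gap is the same in every arm.** Before SR the arms share one hazard; afterwards the true ratio is h. With g in years, the ratio of cumulative hazards over the gap plus 12 months is (g + h)/(g + 1). For h = 1.33 and g = 30/365.25 = 0.082, this is 1.412/1.082 = 1.305. For 15 days (0.041) it is 1.371/1.041 = 1.317.

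**If the gap differed between arms.** With no true difference and an assumed extra 14 days in one arm, the ratio is 1 + 14/365.25 = 1.04, a shift of about 4%. Nothing in the documents shows such a difference.

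**The case against.** The strongest defence is that the conflict hangs on two words. In the follow-up section, the reference to time comes just after a mention of enrolment and could point back to it. All four places then describe one sequence: enrol, give AL, distribute SR. This would remove the contradiction but not the exposure, because that sequence is the one that leaves a gap before SR. The sentence would still need rewording.

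The defence is right on several stronger readings that a reader might infer.

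- *Conflicting exemptions.* The enrolment and follow-up sections give the same 2-week exemption. Section {11d} omits it and states no competing rule.
- *A clash for a recently treated child with a positive RDT.* The exemption concerns the presumptive dose. The enrolment section goes straight on to test-based treatment under national protocols ("unless they have recently been treated (within the last 2 weeks). Participants will be treated according to RDT results"), and the follow-up section does likewise ("Cohort participants who test positive for malaria by RDT will be treated with ACTs free of charge according to national treatment guidelines"). No clash is shown.
- *Bias between arms.* VHTs deliver the product in the VHT arm, while staff make the first delivery in the other two. However, Implementation {16c} makes trained study staff responsible for managing initial deployment everywhere. A differential gap is possible, not shown.
- *Risk time starting at enrolment.* The outcome definition and the 12-month follow-up window both start at SR. This does not, however, remove infections acquired before SR and detected after it.
- *Contaminated baseline incidence.* The pre-deployment incidence is described for study clusters. The text does not say that it comes from cohort children already given AL.

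**Conclusion.** The concern holds as an unresolved timing of the step that sets time zero, with a modest expected effect. Under AL at enrolment, about 2% to 4% of children would carry a pre-SR infection into follow-up with a 2-week gap, and at most 4% to 8% with a full month. These figures rest on assumed gaps and the plan's annual rate, and ignore post-treatment protection.

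A reader might conclude that 10% or more of first infections are at stake. At 30 days the share over the gap plus 12 months is about 10% to 12%, but that needs every child to wait the full month, which no passage says. If SR went out at the end of the month and enrolment were spread evenly, the average gap would be about half a month. One factor points the other way: Trial status expects enrolment in July to August 2024, inside the March to October rainy season given under Study setting, so an annual average may understate risk in those weeks.

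With equal gaps, a true HR of 1.33 would shrink to about 1.31, small against a 90% interval of roughly 0.75 to 1.33. The change is still worth making: it is cheap, and an analysis plan cannot undo the order of AL and SR once children have been dosed.

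**What to change.** 1. Reconcile section {11d}, Enrollment of the cohort and both statements in Follow-up of the cohort to one timing of the clearing dose and one exemption, identical in all three arms. Which clinical rule applies is for the investigators.
2. Record the AL date and the first SR installation date for each child.
3. Keep risk time starting at first SR installation, as the outcome and follow-up sections imply, and bound the mid-point imputation so that it cannot fall before that date.
4. Report the AL-to-SR gap by arm. Step 3 alone does not remove carried-over infections, so this table is needed to judge them.
5. Add a sensitivity analysis that excludes infections first detected at the first post-SR RDT.
6. If the pre-deployment incidence is taken from cohort children already given AL, report the enrolment RDT prevalence as the baseline measure instead.

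The cost is rewording in four places, two dates per child, slightly more analysis, and fewer events in the sensitivity analysis, which will also discard some genuine early post-SR infections.

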#### Cost-effectiveness

We will address issues of cost of implementation by evaluating efficacy in relation to coverage using varied delivery systems. The cost of manufacturing the SR intervention by SCJ will be monitored and documented to model affordable pricing by industry stakeholders to produce next in class SR products ensuring efficacious options for procurement by donor agencies and countries. Projected cost per person protected will comprise product costs based on models using project data (epidemiological, and market) and operational costs. Treatment cost averted using ITNs vs ITNs + SR to the global scale is required for estimating the economic impact. The study will measure the cost of Mosquito Shield implementation in relation to manufacturing, efficacy, and coverage to model projections of cost-effectiveness to incentivize procurers.

### Plans to promote participant retention and complete follow-up {18b}

Participant retention strategies will include participant tracing when they miss appointments, visit reminders, request participants to inform study staff of moves outside or within the study area, foster relationships with participants, provision of study staff contact information for easy communication to alleviate any concerns, and periodic generation of retention rate to evaluate strategies. Utilization of the community structure (e.g., VHTs) will make retention efforts more efficient and effective. A study SOP will be developed to provide more details on retention activities to be conducted by study staff.

### Data management {19}

A combination of standardized paper-based and digital forms (under Android tablets) will be used in Uganda. CRS and UND/Center for Research Computing (CRC) will work together to develop the quantitative forms to be uploaded on Android phones/tablets. All data issuing from the electronic data collection system will follow the same data collection processes outlined in the paragraph below. Any changes to quantitative data forms will need to be agreed by relevant Institutional Review Boards (IRBs), the overall CRS PI (in consultation with CRS’ technical advisors), Infectious Diseases Research Collaboration (IDRC)’s local PI, the CRS country level study Program Manager, and UND’s PI. In the event that all four cannot find a consensus on proposed changes, UND’s PI will make the final decision.

#### Data storage

Any data collected on paper forms (including consent forms) will be scanned and transferred to binders for storage in a secure and locked restricted access area, while all electronic captured data will be archived with a documented history of changes or corrections at the local study site. Using CommCare, CRS and IDRC will collect data which will be securely stored on Android devices and then synchronized to CommCare cloud. Data will then undergo an initial cleaning and de-identification by CRS/IDRC, before being synced to UND’s central database. Data from CRS to UND will be transferred through a dedicated secure sFTP server with password protect access from CRS.

#### Data quality control and quality assurance

Data management staff members will have the responsibility of data verification for accuracy and assuring data collection follows standardized protocols. These activities will promote high quality of data and ensure the trial is performed in compliance with GCP and the applicable regulatory requirement(s). Training on data collection will occur prior to the start of intervention and throughout the trial period with refresher trainings. Standardized data collection forms will be used and source data verification will occur through (1) self-quality checks, making sure data forms are fully completed and (2) data queries, quality checks on a routine basis. In addition, tablet-based digital forms that will be used for data entry will be custom-designed to include rules and conditions for data variable responses (e.g., text responses cannot occur for numeric value, and thresholds for numeric data, etc.).

#### Data sharing

This project will generate considerable data over the course of the 1-year study period. The data management plan will follow the guidelines and suggestions put forward by the NIH in its online guidance document https://humansubjects.nih.gov/data_safety, the WHO Data Sharing Policy https://www.who.int/publications/i/item/9789240044968, and by the respective institutions involved in the research (CRS, IDRC, and UND). The goal is transparent sharing of key findings and data so that the broad impacts of the research are meaningful and useful to key stakeholders and will therefore be shared with stakeholders as may be required.

### Confidentiality {27}

A password-protected central study database warehousing data will be developed and managed by the UND and serve as a data repository and utilized for safe data storage, extraction, integration, and analysis. The data warehouse and file repository will be backed up weekly at the local server level to ease recovery as needed. In addition, data is stored and backed-up on CommCare cloud. Access to study data is controlled through centralized administration and access will be granted to all study investigators through UND PI’s permission. Research records for all study participants including history and physical findings, and results of consultations are to be maintained by the local site PI in a secure storage facility and by the UND and CRS, for a minimum of 5 years after the end of the project or until notified by grantee, and for a maximum of 7 years. Data and samples can be destroyed at any given time after those 5 years.

All records will be kept confidential. Study participants will be identified only by a unique identification number. No individual identities will be used in any reports or publications resulting from the study. All project staff will be trained on procedures for maintaining confidentiality.

